## Abstract

**Background:**

The use of thrombolytic therapy in the treatment of thrombosed infrainguinal native arteries and bypass grafts has increased over the years. Main limitation of this treatment modality, however, is the occurrence of bleeding complications. Low intensity ultrasound (US) has been shown to accelerate enzymatic thrombolysis, thereby reducing therapy time. So far, no randomized trials have investigated the application of US-accelerated thrombolysis in the treatment of thrombosed infra-inguinal native arteries or bypass grafts. The DUET study (Dutch randomized trial comparing standard catheter-directed thrombolysis versus Ultrasound-accElerated Thrombolysis for thrombo-embolic infrainguinal disease) is designed to assess whether US-accelerated thrombolysis will reduce therapy time significantly compared with standard catheter-directed thrombolysis.

**Methods/design:**

Sixty adult patients with recently (between 1 and 7 weeks) thrombosed infrainguinal native arteries or bypass grafts with acute limb ischemia class I or IIa, according to the Rutherford classification for acute ischemia, will be randomly allocated to either standard thrombolysis (group A) or US-accelerated thrombolysis (group B). Patients will be recruited from 5 teaching hospitals in the Netherlands during a 2-year period. The primary endpoint is the duration of catheter-directed thrombolysis needed for uninterrupted flow in the thrombosed infrainguinal native artery or bypass graft, with outflow through at least 1 crural artery.

**Discussion:**

The DUET study is a randomized controlled trial that will provide evidence of whether US-accelerated thrombolysis will significantly reduce therapy time in patients with recently thrombosed infrainguinal native arteries or bypass grafts, without an increase in complications.

**Trial registration:**

Current Controlled Trials ISRCTN72676102

## Background

Thrombosis of an infrainguinal bypass graft or the native lower leg arteries has been associated with a high rate of limb loss and significant morbidity and mortality [1]. Traditional therapy with thrombectomy and eventually additional (bypass) surgery has been associated with moderate long-term patency rates [2]. Catheter-directed thrombolysis was introduced in the early 1980s as a treatment option for occluded bypass grafts. This technique has advantages that make it ideal for acute occlusions, including avoidance of mechanical injury to the endothelium, no need for surgical interventions and more complete lysis of the clot in the bypass graft or outflow arteries. Moreover, it can dissolve platelet-fibrin aggregates in the microcirculation and thrombi in collateral vessels [3].

A recent systematic review that included a meta-analysis of 5 large randomized controlled trials with a total of 1283 patients comparing surgery with thrombolysis in the management of acute lower limb ischemia showed no significant difference between them in limb salvage or death at 30 days, 6 months, or 1 year. However, hemorrhagic complications and distal embolization were more likely at 30 days in thrombolysis patients (8.8% and 12.4%, respectively) than in surgery patients [4,5].

The incidence of these complications might be reduced by a reduction in thrombolytic therapy time. In recent years, ultrasound (US) has been used to accelerate thrombolysis. Low-intensity US-accelerated thrombolysis has been shown to accelerate enzymatic clot lysis in vitro by loosening fibrin strands and thereby increasing thrombus permeability and exposing more plasminogen receptors for binding, without mechanically disrupting the clot [6-8]. The safety of this technique has been shown in the treatment of embolic stroke [9] and deep venous thrombosis [10]. Only two prospective series have been published on the use of US-accelerated thrombolysis in the treatment of thromboembolic obstructions of native arteries and bypass grafts of the lower extremities. In a recent study by Wissgott et al, 25 patients with acute obstructions of the native lower limb arteries were treated with US-accelerated thrombolysis. The technical success rate of 100%, and total clot removal was achieved in 88% of the patients within 24 hours. There were no complications related to the catheter system. At the 1-month follow-up, 2 reocclusions had occurred [11]. Motarjeme et al used US-accelerated thrombolysis in the treatment 24 arterial occlusions and 12 venous occlusions, and complete lysis was achieved in 23 (96%) arterial occlusions. Average time to achieve complete lysis was 16.4 hours (range, 3-25 hours). During the 12-month follow-up, only 1 femoropopliteal graft rethrombosed. No bleeding or other complications occurred [12].

So far, no randomized trials have focused on US-accelerated and standard catheter-derived thrombolysis for arterial thromboembolic disorders of the lower limbs. The DUET (Dutch randomised trial comparing standard catheter-directed thrombolysis versus Ultrasound-accElerated Thrombolysis for thromboembolic infrainguinal disease) study is designed to compare US-accelerated thrombolysis with standard thrombolysis in patients with recently thrombosed infrainguinal native arteries or bypass grafts.

### Hypothesis

We anticipate that US-accelerated thrombolysis will result in a significant reduction in thrombolysis time (12 hours or more), without increasing the complication rate.

## Methods/Design

### Study objectives

The purpose of the study is to demonstrate that US-accelerated thrombolysis will significantly reduce (by at least 12 hours) therapy time compared with standard thrombolysis, without increasing complication rate.

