#### Sample size calculation

The assumption has been made that the mean duration for successful standard thrombolytic treatment of infrainguinal native arteries or bypass grafts is 2.5 ± 1 day, based on retrospective series from the St. Antonius Hospital, Nieuwegein. Given a power of 90% and a 2-tailed significance of 5%, a 2-armed randomized trial including 26 patients in each arm will be needed to prove a significant reduction in therapy time (12 hours or more) with US-accelerated thrombolysis compared with standard thrombolysis. Taking into account 5% to 10% dropouts in each arm, 30 patients need to be included in each study arm. We will analyze the primary outcome by means of Kaplan-Meier and Log-rank test. The sample size calculation is also based on this premise. We will assess imbalance in prognostic factors as a secondary analysis by means of Cox-proportional Hazards multivariate analysis.

An interim analysis on the primary end point (ie, efficacy) will be performed after 50% of patients have completed their follow-up. The Peto approach will be followed, meaning that the study will only be stopped for beneficial effects in case of a *P *< .001 [15]. The study will not be stopped in case of futility. End points in blinded groups will be assessed by the DSMB.

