## Discussion

Several treatment strategies have focused on accelerating thrombolytic therapy to improve its effectiveness and to reduce treatment time and, therefore, adverse effects. US-accelerated thrombolysis, which involves the simultaneous delivery of low-intensity US and a thrombolytic agent into a thrombosed vessel, has been shown to reduce therapy time. The DUET study is designed to compare US-accelerated thrombolysis with standard thrombolysis in patients with recently thrombosed infrainguinal native arteries or bypass grafts.

Only patients with acute lower limb ischemia in class I and IIa, according to the Rutherford classification, will be included in our study, because catheter-directed thrombolysis is the initial treatment chosen in patients with viable or minimally threatened lower limbs. Immediate surgical revascularization is indicated in most patients with acute lower limb ischemia class IIb and III; therefore, these patients will be excluded from the study.

Prolonged thrombolysis therapy might be expected in clots older than 1 week. Most clots that are less than 1 week old can be rather easily and quickly treated with standard catheter-directed thrombolysis or thrombosuction. The additional value of the more expensive US-accelerated thrombolysis in these thrombi may be argued and these are therefore excluded from this study.

Randomization is stratified according to whether a native artery or a bypass graft is occluded, because it has been shown that thrombolysis of a bypass graft will lead to better outcome than thrombolysis of a native artery.

To test our hypothesis, a control angiography should be performed every 12 hours. Therefore, our sample size calculation is based on a reduction in therapy time of 12 hours or more. Control angiographies at 8:00 a.m. and at 8.00 p.m. would have been sufficient. However, in our study protocol we have incorporated an extra control angiography at 2.00 p.m. to measure our primary outcome more precisely and to reduce any unnecessary exposure to thrombolytics in our study participants.

Two vascular surgeons and 2 interventional radiologists from 2 nonparticipating centers will review all angiographies independently. The vascular surgeons and the interventional radiologists will be blinded for patient characteristics and for the results of the initial reports. They will be asked to classify the degree of lysis, ranging from no lysis, partial lysis, to complete lysis (>95% lysis).

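### The aim is worded as demonstrating a reduction of at least 12 hours, but the planned log-rank test can establish only that therapy time is reduced

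*Protocol article*

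**What the plan says.** Three sections of the protocol article make 12 hours part of what the trial is to establish:

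- Hypothesis: the authors anticipate "a significant reduction in thrombolysis time (12 hours or more), without increasing the complication rate".
- Study objectives: the purpose is to "demonstrate that US-accelerated thrombolysis will significantly reduce (by at least 12 hours) therapy time compared with standard thrombolysis".
- Sample size calculation: the stated number of patients is "needed to prove a significant reduction in therapy time (12 hours or more) with US-accelerated thrombolysis compared with standard thrombolysis".

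The test is named in the Sample size calculation section: "We will analyze the primary outcome by means of Kaplan-Meier and Log-rank test". It is two-sided at 5%. No margin of 12 hours is attached to it, and no rule is given in terms of a confidence limit. A Cox model is planned as a secondary analysis.

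Other parts of the article treat the 12 hours differently. The Discussion says that "our sample size calculation is based on a reduction in therapy time of 12 hours or more" and ties this to the interval between control angiographies, so there it is a planning difference. The Abstract and the Conclusion promise evidence on whether therapy time is significantly reduced, with no figure in hours.

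**The concern.** A log-rank test rejects equality of the two time-to-flow curves. It does not reject a gain of, say, 5 hours in favour of a gain of 12 or more. The secondary Cox model yields a hazard ratio, which is not in hours either. The article therefore states two different claims, and only the weaker one matches its test.

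What is at stake is how a significant result would be reported. With this sample size, a barely significant result has a point estimate close to 12 hours. That is the result most likely to be written up as having met the stated objective, although its confidence interval would reach down to about zero.

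**Working it through.** **Inputs.** Sample size calculation section: "mean duration for successful standard thrombolytic treatment of infrainguinal native arteries or bypass grafts is 2.5 ± 1 day", read here as mean 60 h and SD 24 h; 26 evaluable and 30 enrolled per arm; 90% power; two-sided 5%. Two assumptions are mine: ± denotes an SD, and it is equal in both arms. A comparison of means stands in for the log-rank test so that results can be given in hours.

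**The plan's own figure.** For a 12 h difference in means, n per arm = 2 × (1.960 + 1.282)² × (24/12)² ≈ 84.1, so 85. The stated 26 does not reproduce. That is a separate and more serious matter, and nothing below depends on it beyond using 26 and 30 as the planned sizes.

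**Precision.** SE = 24 × √(2/n); half-width = t × SE.

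- n = 30: SE = 24 × √(2/30) = 6.20 h; t(58) = 2.002; half-width 12.4 h.
- n = 26: SE = 24 × √(2/26) = 6.66 h; t(50) = 2.009; half-width 13.4 h.

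**A just-significant result.** The observed gain equals the half-width, 12.4 h or 13.4 h, and the interval runs from about 0 to about 25 h or 27 h.

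**What would show at least 12 hours.** The lower limit must be 12 h or more, so the observed gain must be at least 12 + 12.4 = 24.4 h (30 per arm) or 12 + 13.4 = 25.4 h (26 per arm).

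**Chance of reaching that.** Φ((true gain − 12)/SE − 1.96):

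| True gain | 26 per arm | 30 per arm |
|---|---|---|
| 12 h | 2.5% | 2.5% |
| 18 h | 14% | 16% |
| 24 h | 44% | 49% |
| 30 h | 77% | 83% |
| 36 h | 95% | 97% |

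For example, at 24 h with 30 per arm: Φ(12/6.20 − 1.96) = Φ(−0.02) = 0.49. The 12 h row is simply the one-sided 2.5% error rate of a test against a 12 h margin. It would be the same at any sample size.

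**Check with the log-rank test itself.** I used simulated trials (2,000 per setting; normal, gamma and lognormal times; control mean 2.5 days, SD 1 day, no censoring; 26 or 30 per arm). With a true gain of only 6 h, the test was significant in about 12% to 15% of trials. With a true gain of exactly 12 h, about 4% to 12% of the significant trials had an observed mean gain below 12 h. Significance and a gain of at least 12 hours are thus different findings under the planned test too.

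**The case against.** The strongest reply is that 12 hours is only the planning difference, put in parentheses as common shorthand. The Discussion uses it that way, the Hypothesis section introduces it as something anticipated, and no section sets a null hypothesis of 12 hours or less. This is probably what was intended. It does not remove the point, because the objective speaks of demonstrating the 12 hours and the sample size sentence of proving them.

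Three stronger readings are tempting, and the document does not support them:

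- *A reader might infer that a significant result would not support the trial's stated conclusion.* The Abstract and Conclusion promise only evidence on a significant reduction, and a significant log-rank result in the right direction supports that. The mismatch is with the objective, the hypothesis and the sample size wording.
- *A reader might infer that the plan has no estimate in hours.* Kaplan-Meier curves can give median times by arm, and the summary measure with its interval may well stand in an analysis plan that is not shown. The absence cannot be established from this article.
- *A reader might infer that a gain of at least 12 hours is out of reach.* The 2.5% at a true gain of 12 h says nothing specific about this trial. The Background cites a series with a mean lysis time of 16.4 h under ultrasound. Set against the assumed 60 h for control, that is a gain of 43.6 h, and with SE 6.20 h the chance of a lower limit above 12 h is Φ(31.6/6.20 − 1.96), above 99%. The comparison is not randomized, but large gains cannot be ruled out.

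**Conclusion.** The point stands as a defect of wording and of permitted inference. The log-rank test remains valid for superiority, and nothing here calls for a change in design, test or conduct. The aim as worded in three sections goes beyond what that test can establish.

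As for size, an observed gain of roughly 24 to 25 h is needed before gains below 12 h are excluded, whereas significance needs only about 12 to 13 h. Results between those two values would be significant and still fall short of the objective. How often the stronger claim could be made depends on the unknown true gain: 44% to 49% of the time at 24 h, and about 95% or more at 36 h. These figures rest on ± 1 day being an SD, on equal SDs in the two arms, and on a comparison of means as an approximation to the planned analysis.

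**What to change.** 1. Reword the aim in the Hypothesis, Study objectives and Sample size calculation sections as superiority, meaning any reduction in therapy time. Name 12 hours as the difference used for planning, as the Discussion already does.
2. State that the between-arm difference will be reported in hours with a 95% confidence interval. A difference in restricted mean time with a truncation time fixed in advance would serve, as would a difference in Kaplan-Meier medians. If the analysis plan already specifies such an estimate, a reference to it is enough.
3. Allow the claim of a reduction of at least 12 hours only if the lower confidence limit is 12 hours or more.

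The cost is some rewording, one extra estimate and a more modest permitted claim. The alternative is to keep the objective as worded and test against a 12 h margin. Under the same assumptions, 90% power would then need 2 × (1.960 + 1.282)² × 24²/(true gain − 12)² patients per arm: 85 at a true gain of 24 h and 337 at 18 h. Rewording is therefore the proportionate choice.

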### Primary endpoint

The primary end point is the duration of catheter-directed thrombolysis needed for uninterrupted flow in the thrombosed infrainguinal native artery or bypass graft with outflow through at least 1 crural artery.

### Secondary endpoints

1. Technical success, defined as complete lysis of the thrombus of the native artery or bypass graft, without distal thromboembolic complications

2. Number of units of urokinase needed for uninterrupted flow in the thrombosed infrainguinal native artery or bypass graft with outflow through at least 1 crural artery

3. Thrombolysis-induced hemorrhagic complications

4. Thirty-day mortality

5. Duration of hospital admission

6. Costs of hospital admission

7. Thirty-day patency of the target native artery or bypass graft, as evidenced by magnetic resonance angiography (MRA)

8. Drop of serum fibrinogen concentration to below 1.0 g/L during procedure

9. Conversion to open surgery

10. Distal thromboembolic complications

11. Other complications

### Definitions

Complete lysis: clot lysis of >95% determined by arteriographic measurements of the thrombosed native arterial segment or bypass graft [13].

Hemorrhagic complications are defined as:

• hemorrhagic complication requiring interruption or ending of thrombolysis

• hemorrhagic complication requiring surgical intervention

• hemorrhagic complication requiring transfusion

Rutherford classification of acute limb ischemia [14]:

Class I: Viable--not immediately threatened, no sensory loss or muscle weakness, arterial Doppler signal is audible

Class IIa: Marginally threatened--salvageable if promptly treated, minimal sensory loss, no muscle weakness, arterial Doppler signal is often inaudible

Class IIb: Immediately threatened--salvageable with immediate revascularization, sensory loss associated with rest pain in more than the toes, mild to moderate muscle weakness, arterial Doppler signal is usually inaudible.

Class III: Irreversible--major tissue loss or permanent nerve damage inevitable if there is significant delay before intervention, profound limb anaesthesia and paralysis, arterial and venous Doppler signal is inaudible

### Design of study

This is a multicenter 2-group parallel randomized trial.

### Setting

Patients who will meet the inclusion criteria will be enrolled from 5 teaching hospitals in the Netherlands.

### Patients

A total of 60 adult patients with acute lower limb ischemia due to recently (between 1 and 7 weeks) thrombosed infrainguinal native arteries or bypass grafts will be randomized.

### Eligibility criteria

#### Inclusion criteria

1. Men and women older than 18 years and younger than 85 years old

2. Patients with recently (between 1 and 7 weeks) thrombosed femoropopliteal or femorocrural native arteries or femoropopliteal or femorocrural venous or prosthetic bypass grafts with ischemic complaints

3. Patients with acute lower limb ischaemia class I and IIa according to the Rutherford classification

4. Patients understand the nature of the procedure and provide written informed consent before enrollment in the study

#### Exclusion criteria

1. Patients with isolated common femoral artery thrombosis, including the origin of the superficial femoral artery and profunda femoral artery

2. Patients with localized (less than 5 cm) emboli or occlusions in the native femoropopliteal arteries

3. Patients with clinical complaints of acute lower limb ischemia due to thrombosis of the femoropopliteal or femorocrural native arteries, or femoropopliteal or femorocrural venous or prosthetic bypass grafts less than 1 week and more than 7 weeks

4. Patients with acute lower limb ischemia class IIb and III according to the Rutherford classification

5. Patients for whom antiplatelet therapy, anticoagulants, or thrombolytic drugs are contraindicated

6. Recent (less than 6 weeks) ischemic stroke or cerebral bleeding

7. Patients with recent (less than 6 weeks) surgery

8. Severe hypertension (diastolic blood pressure greater than 110 mm Hg, systolic blood pressure greater than 200 mm Hg)

9. Current malignancy

10. Patients with a history of prior life-threatening reaction to contrast medium

11. Patients with uncorrected bleeding disorders (gastrointestinal ulcer, menorrhagia, liver failure)

12. Women with child-bearing potential not taking adequate contraceptives or currently breastfeeding

13. Pregnancy

14. Patients considered hemodynamically unstable at the onset of the procedure

15. Patients who refuse treatment

16. Patients who are currently participating in another investigational drug or device study who have not completed the entire follow-up period

17. Patients younger than 18 years or older than 85 years

18. Severe comorbid condition with a life expectancy of less than 1 month

19. Contraindication for magnetic resonance imaging (MRI)

### Randomization

Central randomization will take place using a computerized randomization procedure. Block-randomization is used and stratified according to whether a native artery or a bypass graft is involved. Blinding will not be used.

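### The primary log-rank test is named without the native-artery/bypass-graft stratum used in randomisation; stratifying it guards against a loss of power at almost no cost

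*Protocol article*

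**What the plan says.** All statements are in the protocol article.

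- Randomization section: "Block-randomization is used and stratified according to whether a native artery or a bypass graft is involved".
- Discussion section, as the reason for stratifying: "thrombolysis of a bypass graft will lead to better outcome than thrombolysis of a native artery". No size is given, and the outcome meant is not identified as time to lysis.
- Sample size calculation section, on the primary analysis: "We will analyze the primary outcome by means of Kaplan-Meier and Log-rank test". The stratum is not mentioned, and the sample size is said to rest on the same analysis.
- Same section, on adjustment: "We will assess imbalance in prognostic factors as a secondary analysis by means of Cox-proportional Hazards multivariate analysis". The stratification factor is not named and no covariate list is given.
- Same section, on planning values: "the mean duration for successful standard thrombolytic treatment of infrainguinal native arteries or bypass grafts is 2.5 ± 1 day" and "a 2-armed randomized trial including 26 patients in each arm will be needed", raised to 30 per arm for dropout. The single pooled duration makes no distinction between native arteries and grafts.

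**The concern.** When randomisation is stratified on a factor that predicts the outcome, the arms are more alike than under simple randomisation. The ordinary log-rank variance takes no credit for this. It is therefore too large, the test rejects too rarely under the null, and power is lost. Pooling patients with different baseline hazards also pulls the marginal hazard ratio towards 1.

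The secondary Cox analysis does not clearly make up for this. It is directed at imbalance, and stratified blocks keep precisely this factor balanced. An analysis prompted by imbalance has least reason to include the one factor that the article itself gives a prognostic reason for.

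At stake is a missed effect in a trial of 60 patients, and a somewhat diluted effect estimate. No false-positive risk is at stake.

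**Working it through.** **1. The plan's own figure, used to choose a treatment effect.** Inputs: 90% power, two-sided 5%, difference 0.5 day, SD 1 day (Sample size calculation section). For two means, n per arm = 2(z₀.₉₇₅ + z₀.₉₀)²·SD²/δ² = 2(1.960 + 1.282)²/0.25 = 84.1, so 85. The stated 26 is not reproduced. That is a separate matter from the present point. To study the test where the trial would have its claimed power, take 26 per arm as 52 events in Schoenfeld's formula: |ln HR| = 2(1.960 + 1.282)/√52 = 0.899, so HR = 2.46 for reaching flow.

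**2. The two tests.** Both use Z = Σ(O − E)/√ΣV. The unstratified test forms E and V from one pooled risk set. The stratified test forms them within native arteries and within grafts, then adds.

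**3. Simulation under proportional hazards.** 60 patients, permuted blocks of 4 within stratum, exponential times, all reaching flow, critical value 1.96, 4,000 runs per cell. Block size, graft share and stratum HR are assumptions, because the article gives none of them. With every patient reaching flow and no ties, the log-rank test uses only ranks, so the baseline shape does not matter. Entries are percentages; differences are taken before rounding.

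| Graft share | Stratum HR | Type I error, unstratified / stratified | Power at HR 2.46, unstratified / stratified | Gain from stratifying |
|---|---|---|---|---|
| 50% | 1 | 5.9 / 5.9 | 92.2 / 91.4 | −0.8 |
| 50% | 1.5 | 5.8 / 5.9 | 90.2 / 89.8 | −0.4 |
| 50% | 2 | 4.5 / 5.4 | 87.7 / 90.2 | +2.5 |
| 50% | 3 | 3.8 / 5.4 | 82.9 / 90.4 | +7.6 |
| 50% | 5 | 2.5 / 5.5 | 73.3 / 89.5 | +16.2 |
| 30% | 1 | 5.5 / 5.6 | 91.2 / 89.8 | −1.4 |
| 30% | 1.5 | 5.4 / 5.9 | 90.1 / 90.2 | +0.1 |
| 30% | 2 | 5.0 / 5.5 | 89.8 / 91.3 | +1.5 |
| 30% | 3 | 4.2 / 5.7 | 86.0 / 90.9 | +4.9 |
| 30% | 5 | 3.5 / 5.9 | 81.2 / 90.6 | +9.5 |

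Simulation error is about 0.3 points for type I error and at most 0.8 for power. Both tests run slightly above 5% when the stratum has no effect, so that excess is not caused by stratifying.

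**4. A second simulation.** Weibull times with shape 2.7, strata balanced within arm, half grafts, 2,500 runs. At treatment HR 2.46, stratifying raises power from 89% to 91% (stratum HR 2) and from 82% to 90% (stratum HR 3). The unstratified type I error at stratum HR 3 is 3.4%. At treatment HR 1.83, which is what means of 2.5 and 2.0 days imply for this shape (1.25^2.7 = 1.83), power rises from 54% to 60% and from 47% to 60%. More points are at risk when power is in the middle of its range.

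**5. A check on the plan's own scale.** Normal times with mean 60 h and total SD 24 h, read at the scheduled angiographies; half grafts; true reduction 12 h. The total SD is held at 24 h, so a wider gap between strata leaves less spread within them: for a 24 h gap, √(24² − 0.25·24²) = 20.8 h.

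| Gap between strata | Unstratified type I error | Power, unstratified / stratified |
|---|---|---|
| 0 h | 5.9 | 42.8 / 42.1 |
| 12 h | 4.9 | 44.0 / 45.3 |
| 24 h | 3.0 | 42.8 / 54.9 |
| 36 h | 0.8 | 41.7 / 77.0 |

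The pattern is the same: no material difference for a small gap, a clear one for a large gap.

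**The case against.** The strongest objection is that the article never says the log-rank test is unstratified. It condenses a fuller protocol, and an analysis plan that is not shown could specify stratification. A reader might infer that the trial has committed itself to an unstratified test; the text does not go that far. What stands against the objection is that the article does more than stay silent. It names the primary test without the stratum and assigns prognostic factors to a secondary analysis, so the design factor is not carried into the primary test where one would look for it.

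A second objection concerns size. A reader might infer that graft versus native artery is a strong predictor of lysis time, so that power is certainly being thrown away. The documents do not support this. The Discussion speaks only of a better outcome, which could mean patency or limb salvage, and the planning duration is pooled over both vessel types. For a stratum HR up to 1.5 there is nothing to gain. This objection stands, and it makes the loss conditional.

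A third concerns the secondary model. A reader might infer that the data will select the covariates. The article states no selection rule, and a covariate list is ordinary analysis-plan content. What can be said is only that the stratum is not named and that the stated aim gives no assurance it will be included.

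Finally, the dilution of the hazard ratio carries limited weight: the article names no HR as its primary estimate, and a marginal HR differs from a stratum-specific one partly because it is a different quantity.

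**Conclusion.** The point holds as a conditional one. The protocol stratifies randomisation on a factor it regards as prognostic and does not carry that factor into its named primary test. If the factor predicts time to lysis and the test is run unstratified, the test is conservative and loses power. At a treatment HR of 2.46 with 60 patients, the loss is under 2 points for a stratum HR up to 1.5, about 1 to 3 points at 2, and about 5 to 8 points at 3. Type I error in that last case is about 3.4-3.8% with half grafts. With no stratum effect, stratifying costs about 1 point (0.8 and 1.4 in the two graft shares tried). These figures assume proportional hazards, all patients reaching flow, and a graft share of 30% or 50%.

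The error is in the conservative direction, so a positive result is not put in doubt. Nor does this point account for the trial's power problem: with 30 per arm, power for a 12 h difference at SD 1 day is about 49%, and that shortfall comes from the sample size calculation. This is a nearly free improvement. Confidence is high on the direction of the effect and medium on the size of the gain.

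**What to change.** - Name as the primary test a log-rank test stratified by native artery versus bypass graft, and report the hazard ratio from a Cox model stratified the same way. If an unstratified test is intended, say so and give the reason.
- In the secondary Cox analysis, always include the stratum, whatever the observed imbalance.

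The cost is a sentence or two in the protocol or analysis plan, written before outcome data are compared by arm. It needs no further patients or data, because vessel type is already recorded at randomisation. The statistical cost if the stratum turns out not to matter is about 1 power point.
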